### Sample size

During an extensive literature search, no randomized clinical trials were found that investigated the effect of MHM on CHF in post stroke patients. Thus, it was decided to use a study that investigated the effects of a physiotherapy technique on ICP for the sample calculation.

To obtain the sample size needed for this study, we used the combination of statistical software’s R and G-Power 3.1. First, we extracted the intracranial pressure with the techniques performed in the study bellow [28]. From this previous work, we detected that the median value of ICP for the control group was 16.9, and for the intervention group, it is 11.7. Then, we calculated the Cohen-D effect size from the medians using the package ‘rcompanion’ in R [29]. The final step using the GPower is where we estimate with a power of 95% and a confidence level of 95% the minimum sample size for a *T-Student* equivalence test [30]. The total number of subjects is 60, equally distributed in two groups of 30 patients.

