## Methods

### Trial design

The protocol complies with a randomized controlled equivalence trial, double-blinded, parallel (1:1 ratio), and exploratory approved by the Research Ethics Committee of the Hospital de Clínicas of the Universidade Federal do Parana (CAAE: 01,378,118.7.0000.0096). The individuals are allocated through simple randomization into two groups. All items in the Data Set of the Register of Tests by the WHO were recorded on the database of the Brazilian Clinical Trial Registry (RBR – 5qs9k2n). Any alteration in the protocol is informed to the above-mentioned bodies. When preparing this protocol, we used the SPIRIT reporting guidelines [17], and a table with the standard protocol items (SPIRIT) is presented in Table 1. The SPIRIT checklist is available as an additional file (Additional file 1).

**Table 1 Tab1:** Time schedule of enrollment, interventions, assessments, and visits for participants according to Recommendations for Interventional Trials (SPIRIT)

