### Primary outcome

#### Intracranial compliance

The ICC of all participant patients will be measured in a non-invasive manner through the sensor in the ICP equipment B4C BcMM-R-2000, acquired through funding by the National Council of Research. The researchers were trained by the B4C company and are prepared for data collection. To proceed with the monitoring, a sensor is installed by the researcher coupled to the scalp using an elastic band, without requiring any prior preparation or trichotomy.

The sensor is coupled through wires to a monitor that generates a curve and real-time display of ICP wave, in addition to recording the data for further analysis, which is enabled by extensometers capturing the intracranial volume expansions, since the cranial bone is not entirely hard. Therefore, the pulses are converted into numerical data forming the ICP curve morphology in real time [22].

The ICP wave morphology has its layout, such as in the case of the arterial pulse wave, with a total of up to five distinct peaks, of which three are proper and frequent: percussion wave (P1), tidal wave (P2), and dichroic wave (P3). P1 wave is the most constant in amplitude and derives from the pulse of large cerebral arteries to the choroid plexus. P2 wave, in turn, originates from the cerebral elastance direct reflecting the “reverberation” of P1 on both the brain and cranium, that is, ICC. Finally, the P3 wave is separated from P2 by the dicrotic notch corresponding to the closure of the cardiac aortic valve [23].

The analysis system checks all collected data and analyzes it using a previously created algorithm. The data collected by this sensor are qualitative, which means that the ICP has no absolute value; however, it is possible to analyze the morphology of this pressure curve by extracting three values: P2/P1 ratio, TTP, and pulse amplitude. For this study, all calculations were performed from the average of pulses within each minute of monitoring after excluding possible artifacts. These averages were used to calculate the amplitudes of the two main peaks in the wave morphology, P2 and P1. The P2/P1 ratio was calculated by dividing the amplitudes of the two peaks and the TTP by the time interval from the beginning of each pulse to the peak [15].

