### Statistical methods

The collected data will be organized on a spreadsheet and summarized using techniques of descriptive statistical analysis. The qualitative variables will be summarized by building frequency tables and the quantitative variables by calculating the descriptive measures (average, mean, standard deviation, and percentiles 25–75).

The evaluations’ primary outcome and secondary outcomes will be made in 5 different times; for that, the data will be analyzed by analysis of variance (ANOVA) two-way for repeated measures with the Tukey post-test for results that present normal distribution and homogeneity of variances, verified by the test of Shapiro–Wilk and Average in Levene, respectively.

We will be using the statistical software Statistical Package for the Social Sciences (SPSS) (IBM—version 22) to analyze the collected data. Our research hypotheses will be tested using non-parametric methods. Wilcoxon test with Kruskal–Wallis post-test will also be applied (intergroups). The level of significance established was *p* ≤ 0.05. The evaluation of results and data analysis will be carried out by an independent professional.

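### The stated 95% power is not established for the trial's equivalence question: it rests on a 5.2-unit median ICP difference from another technique, with no margin or SD on the primary outcome

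*Protocol article*

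**What the plan says.** The Sample size section explains that no randomized trial of the maneuver was found, so a study of a different physiotherapy technique and its effect on ICP was used instead. From that study, "we detected that the median value of ICP for the control group was 16.9, and for the intervention group, it is 11.7". Next, "we calculated the Cohen-D effect size from the medians", using an R package. The last step, in G-Power, was run "with a power of 95% and a confidence level of 95% the minimum sample size for a" Student t equivalence test. The result is 60 patients, 30 per arm. The section reports no value of d, no SD or other measure of spread, and no equivalence margin.

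The Intracranial compliance section under Primary outcome defines what is measured. "The data collected by this sensor are qualitative, which means that the ICP has no absolute value"; the wave is summarised by three values, the P2/P1 ratio, TTP and pulse amplitude. The same part of the article names T2 as the most relevant time for the primary outcome.

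Trial design calls the study a 1:1 parallel equivalence trial and also exploratory. The Abstract expects no change in intracranial compliance.

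**The concern.** An equivalence calculation needs three inputs on the scale of the primary outcome: a margin, an SD, and an assumed true difference, usually zero or close to it. The article supplies one input, an observed between-group difference, and it is on a scale that this trial does not measure. Nothing links a standardised effect on absolute ICP to the variability of P2/P1, or to the largest change in P2/P1 that would be tolerable.

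The trial hopes to support the safety of a maneuver in ventilated stroke patients. A reader told that it is an equivalence trial with 95% power will take a finding of no difference as strong reassurance. How strong it is depends on a margin that the calculation does not state.

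**Working it through.** **Inputs from the article.** Medians 16.9 and 11.7, so the difference is 16.9 − 11.7 = 5.2 (no unit given). Power 95%, confidence 95% (sidedness not stated), 30 per arm. Not given: d, SD, margin.

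**Can 60 be reproduced?** Not forwards, because d, SD and margin are missing. The only route is to solve backwards.

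*Reading A: 5.2 is a difference to detect.* Exact noncentral t, df = 58, noncentrality d√(30/2), power 0.95:
- two-sided 5%: d = 0.947, so the SD would be 5.2 / 0.947 = 5.49
- one-sided 5%: d = 0.860, so the SD would be 5.2 / 0.860 = 6.05

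*Reading B: 5.2 is the equivalence margin.* Two one-sided tests (TOST), true difference 0, power integrated over the distribution of the sample SD (df = 58), power 0.95:
- 5% per side: margin = 0.942 SD, so the SD would be 5.2 / 0.942 = 5.52
- 2.5% per side: margin = 1.029 SD, so the SD would be 5.2 / 1.029 = 5.05

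A two-sided 5% difference test and TOST at 5% per side share one normal approximation, n per arm = 2 × [SD × (1.645 + 1.960) / 5.2]². The result 30 therefore does not show which was run. Over a range of assumed ICP SDs:

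| Assumed SD | 3 | 4 | 5 | 5.5 | 6 | 7 | 8 | 10 |
|---|---|---|---|---|---|---|---|---|
| n per arm | 9 | 16 | 25 | 30 | 35 | 48 | 62 | 97 |

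On these readings 30 per arm fits an SD of roughly 5 to 6, which the article does not state. Reading A gives power to detect a difference, not to show equivalence. Reading B gives equivalence power, but on absolute ICP. Neither gives power for P2/P1.

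**What 30 per arm delivers on any continuous outcome.** TOST at 5% per side, true difference 0, margin in SD units of that outcome:

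| Margin (SD) | 0.3 | 0.5 | 0.7 | 0.8 | 0.9 | 1.0 |
|---|---|---|---|---|---|---|
| Power at 30 per arm | about 0% | 21% | 70% | 84% | 93% | 97% |
| n per arm for 95% power | 290 | 105 | 54 | 42 | 33 | 27 |

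Solving for the margin gives 0.942 SD at 95% power and 0.765 SD at 80% (0.7646 before rounding, quoted as ±0.76).

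**With adjustment for the pre-maneuver value.** The residual SD shrinks by √(1 − r²), so the margin for 95% power is 0.942 × √(1 − r²). The correlation r is an assumption:
- r = 0.3: 0.942 × 0.954 = 0.90 SD
- r = 0.5: 0.942 × 0.866 = 0.82 SD
- r = 0.7: 0.942 × 0.714 = 0.67 SD
- r = 0.8: 0.942 × 0.600 = 0.57 SD

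**What the confidence interval can exclude.** The 90% interval half-width is t(0.95; 58) × √(2/30) = 1.672 × 0.258 = 0.43 SD. A true difference exactly equal to the margin is declared equivalent 5% of the time.

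**The case against.** The article openly says that a stand-in study was used because none existed for this maneuver, and it calls the trial exploratory. Cohen's d has no units, so carrying it from ICP to another outcome is not absurd in itself. The text names an equivalence test, so it cannot be asserted that a superiority calculation was run. The SD near 5.5 is inferred from n, not documented, and 60 is not shown to be an arithmetic error. With a justified P2/P1 margin of 0.94 SD or more, 30 per arm would have its 95% power. All of this stands. It limits the conclusion to power that is not established. It does not rescue the 95%, because disclosing a proxy supplies neither a margin nor a reason why the standardised effect should carry over to waveform morphology.

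Two stronger readings are tempting and should be avoided.
- A reader might infer that, with a 5.2-unit margin, an effect as large as the earlier one would count as equivalent. It would not: a true effect at the margin passes only 5% of the time. At the inferred SD of 5.5 the 90% half-width is 0.43 × 5.5 ≈ 2.4, so the observed difference would have to be below about 5.2 − 2.4 = 2.8 to pass.
- A reader might infer that the trial can exclude only differences of about one SD. That confuses the margin needed for 95% power with what the interval excludes: an observed difference near zero would exclude anything beyond about 0.43 SD.

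**Conclusion.** The concern holds in this form: the 95% power is not established for equivalence on the primary outcome. It comes from an observed 5.2-unit ICP difference under another technique, with d, SD and margin unreported, while the sensor yields no absolute ICP. The sample size of 60 cannot be reproduced from the stated inputs, and the text does not show whether 5.2 served as a difference to detect or as a margin. Neither use supports 95% power on P2/P1.

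The size of the problem depends on the margin. Unadjusted, power at 30 per arm runs from 21% at ±0.5 SD to 95% at ±0.94 SD. These figures assume normal data, equal SDs, a true difference of zero, 5% per side and 30 analysed patients in each arm. The documents do not support saying that the trial is underpowered, since no margin is stated against which to judge it. The same gap applies to TTP and pulse amplitude.

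**What to change.** Keep n = 60. In the Sample size section, remove the ICP-median justification and the unqualified 95% power, and state what 30 per arm delivers for P2/P1 at T2 under TOST at 5% per side with a true difference of 0: 95% power at ±0.94 SD, 80% at ±0.76 SD, 70% at ±0.7 SD and 21% at ±0.5 SD. If the analysis will adjust for the pre-maneuver value, give the 95% margin over a range of correlations (±0.90, ±0.82, ±0.67 and ±0.57 SD for 0.3, 0.5, 0.7 and 0.8), not at one assumed value.

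Fix the P2/P1 margin on clinical grounds before any unmasked analysis. Take the SD from pooled, arm-masked pre-maneuver P2/P1 data; recruitment began in March 2019, so such data should exist. Use only values recorded before the ventilator settings change, because the text under Fig. 2 uses T1 both for the time before the maneuver and for the period in which it is applied. Say that the pre-maneuver SD stands in for the SD at T2. Then report the power at the chosen margin.

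The cost is one rewritten paragraph and a masked SD estimate, with no further patients. The downside is that the stated power becomes less favourable for any tight margin.

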### Statistical methods

The collected data will be organized on a spreadsheet and summarized using techniques of descriptive statistical analysis. The qualitative variables will be summarized by building frequency tables and the quantitative variables by calculating the descriptive measures (average, mean, standard deviation, and percentiles 25–75).

The evaluations’ primary outcome and secondary outcomes will be made in 5 different times; for that, the data will be analyzed by analysis of variance (ANOVA) two-way for repeated measures with the Tukey post-test for results that present normal distribution and homogeneity of variances, verified by the test of Shapiro–Wilk and Average in Levene, respectively.

We will be using the statistical software Statistical Package for the Social Sciences (SPSS) (IBM—version 22) to analyze the collected data. Our research hypotheses will be tested using non-parametric methods. Wilcoxon test with Kruskal–Wallis post-test will also be applied (intergroups). The level of significance established was *p* ≤ 0.05. The evaluation of results and data analysis will be carried out by an independent professional.

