**Discussion:**

This study will be the first clinical trial to examine the effects and safety of MHM on intracranial compliance measured by non-invasive monitoring. Limitation includes the impossibility of blinding the physical therapist who will supervise the interventions. It is expected with this study to demonstrate that MHM can improve respiratory mechanics and hemodynamic parameters and provide a safe intervention with no changes in intracranial compliance in stroke patients.

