In scenarios of normality of ICP and ICC, there is a proportion between the peaks, where P1 > P2. However, in situations of abnormality, there is a change in the morphology of the ICP waveform, with an increase in ICP associated with a low ICC, with P2 > P1. For the TPP variable, the higher the value found, the greater the chance of the peak being P2, which also corresponds to a decrease in the ICC [22, 23].

In this study, the evaluations will be carried out in five (T1–T5) moments:T0: start monitoring, the interval between T0 and T1 is intended to ensure patient stabilization for the start of data collection;T1: capture initial patient data;T2: assess whether the MHM protocol had effects on ICC;T3: verify whether aspiration combined with MHM could lead to different effects on outcomes;T4 and T5: check whether there was stabilization of parameters related to ICC and respiratory mechanics.

The moment of evaluation T2 is the most relevant for the primary outcome; as for the secondary outcomes, evaluations from T2 to T5 are the most relevant.

Data will be collected through a monitor and analyzed using the Brain4care Analytics System, considering that at a time interval, the software selects an average of pulses to form the waves.

To capture the data, the ICP assessment sensor will be chosen according to the cranial circumference (S, M, L, XL) considering as protocol the lowest sensor possible with reading, following the manufacturer’s recommendations. Data collection will start after the coupling procedure and confirmation by the assessor of reading compatible with the acceptable ICP curves.

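### The trial is declared and sized as an equivalence trial, but its stated analysis contains only tests of difference and no equivalence margin, so it cannot support a conclusion of unchanged intracranial compliance

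*Protocol article*

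**What the plan says.** The title and the Trial design section set the objective: "The protocol complies with a randomized controlled equivalence trial, double-blinded, parallel (1:1 ratio), and exploratory". The Discussion paragraph of the Abstract gives the expected conclusion, that the maneuver will "provide a safe intervention with no changes in intracranial compliance in stroke patients". The closing paragraph of the main Discussion repeats the expectation of safety.

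The Sample size section names a Student t equivalence test with 95% power and 95% confidence and arrives at 60 patients, 30 per group. Its effect size is a Cohen d computed from median intracranial pressures of 16.9 and 11.7 in an earlier physiotherapy study. It prints no SD, no value of d and no margin.

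The Statistical methods section then fixes the analysis. For approximately normal data, "the data will be analyzed by analysis of variance (ANOVA) two-way for repeated measures with the Tukey post-test". In addition, "Wilcoxon test with Kruskal–Wallis post-test will also be applied (intergroups". The threshold is "The level of significance established was *p* ≤ 0.05".

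Under Intracranial compliance, the primary outcome is described through waveform measures: "it is possible to analyze the morphology of this pressure curve by extracting three values: P2/P1 ratio, TTP, and pulse amplitude". The same section singles out a time point: "The moment of evaluation T2 is the most relevant for the primary outcome".

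**The concern.** An equivalence claim needs a null hypothesis that the groups differ by at least a stated margin, which the data must then reject. ANOVA, Tukey, Wilcoxon and Kruskal–Wallis work the other way. Their null is no difference, and failing to reject it is not evidence that the null is true. The test named for the sample size is not carried into the analysis, so the two sections disagree about what the trial will test.

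The harmful error here is to conclude that compliance is unchanged when it has worsened, in ventilated patients with acute stroke. The Introduction itself says that hyperinflation raises intrathoracic pressure and can influence intracranial pressure. Under a difference test, smaller numbers, missing readings or noisier measurements make a non-significant result more likely. If that result were taken as reassurance, poorer data would make reassurance easier to obtain.

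**Working it through.** **Step 1. Is there a margin or an equivalence rule anywhere?**

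- Statistical methods: tests of difference only.
- Hemodynamic stability: limits of 20 mmHg, 20 bpm and SpO2 90%. These belong to secondary outcomes.
- Intracranial compliance: P2 > P1 marks an abnormal waveform. It classifies a pulse and is not a tolerated difference between groups.
- Sample size: 16.9 − 11.7 = 5.2 is a difference observed in another study, not a tolerated one. It is also in absolute intracranial pressure, which the article says this sensor does not give.

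None of these is an equivalence margin for the primary outcome.

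**Step 2. Can N = 60 be reproduced?** Not directly, because the SD, d and margin are not given. Solving backwards for 30 per arm and 95% power:

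- Two-sided 5% test of difference: d = 0.947, so SD = 5.2 / 0.947 ≈ 5.5.
- Two one-sided tests (TOST) at 5% each, true difference 0: margin ≈ ±0.94 SD.

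The stated size fits either reading, so it does not reveal which margin, if any, was meant.

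**Step 3. What does a non-significant result mean with 30 per arm?** Simplification: one two-sided t comparison at one time point, alpha 0.05. The noncentrality is d√(n/2) = d√15, with 58 degrees of freedom and critical value 2.002. For d = 0.5 the noncentrality is 0.5 × 3.873 = 1.94, and P(|t| < 2.002) = 0.52.

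**Step 4. What would TOST do at the same true differences?** TOST declares equivalence if |observed difference| + t(0.95, 58) × s × √(2/n) < Δ. With s = 1 SD the half-width of the 90% confidence interval is 1.672 × 0.258 = 0.43 SD.

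| True difference | Difference test non-significant | TOST at ±0.94 SD declares equivalence |
|---|---|---|
| 0.3 SD | 79% | 79% |
| 0.5 SD | 52% | 52% |
| 0.7 SD | 24% | 23% |

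The columns nearly coincide. At a margin that 30 per arm can support with 95% power, changing the test alone alters little. The protection comes from stating a margin and having it judged.

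**Step 5. What margin can 30 per arm support?** TOST power with true difference 0, alpha 0.05 per side and no covariate adjustment, integrating over the sample SD. As a hand check, 2Φ((Δ − 0.432)/0.258) − 1 gives nearly the same values.

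| Margin | Power, 30 per arm | n per arm for 95% power |
|---|---|---|
| ±0.94 SD | 95% | about 30 |
| ±0.8 SD | 84% | 42 |
| ±0.5 SD | 21% | 105 |
| ±0.3 SD | 0% | 290 |

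**Step 6. Effect of data loss.** If only 20 per arm had usable data (an assumption), a true 0.5 SD difference would be non-significant 66% of the time instead of 52%, and a true 0.7 SD difference 42% instead of 24%. Under TOST the interval widens and the claim becomes harder to make.

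**The case against.** Four points can be made for the other side.

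- **No written rule.** A reader might infer that the plan says p > 0.05 will count as proof of no change. It does not. The Abstract and Discussion state expectations, not a decision rule. This stands, and the point is limited to what the listed methods can support.
- **The trial is also called exploratory, and the article condenses a fuller protocol.** A missing margin alone could be condensation. But the article does state its analysis, down to post-tests, assumption checks and software version, and that analysis is of a different kind from the test used to size the trial. The exploratory label sits in the same sentence as the equivalence label and does not support a conclusion of safety.
- **The error is not unlimited.** It is tempting to set the 79%, 52% and 24% against a 5% false-equivalence rate for TOST and call the present error uncontrolled. That comparison is unfair: the 5% applies only when the true difference equals the margin. At ±0.94 SD, TOST declares equivalence about as often at these same differences. If the assumed SD held, 95% power would also keep the chance of missing a difference of about 0.95 SD near 5%. This stands.
- **The figures simplify.** They model one t comparison. The power of the repeated-measures ANOVA also depends on a within-patient correlation that is not given. This stands too, but the mismatch between objective and test does not depend on the figures.

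**Conclusion.** The point holds: objective and sample size are framed as equivalence, the analysis is framed as difference, and no margin links them. As written, the analysis cannot support a conclusion that intracranial compliance is unchanged, whatever p-value it returns. As an indication of size, a true 0.5 SD difference would be non-significant in 52% of trials with 30 per arm. This assumes a single two-sided 5% t comparison, equal SDs and complete data.

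The article does not support the further reading that the investigators have committed to treating non-significance as equivalence, or that replacing the test would by itself bring false reassurance down to 5%. What matters is whether a margin that is defensible for these patients is also one that 30 per arm can test. The article gives no basis for answering that.

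**What to change.** - **Primary analysis.** Estimate the experimental minus control difference in one named compliance measure (for example P2/P1) at T2, adjusted for the T1 value. State the role of time to peak and pulse amplitude, which the article also lists for this outcome. Keep the ANOVA and rank-based tests as supportive.
- **Decision rule.** Claim equivalence only if the 90% confidence interval for that difference (two one-sided 5% tests) lies wholly within ±Δ.
- **Margin.** Justify Δ on clinical or external grounds and fix it before unblinding. Do not derive it from the trial's own T1 data. A rule based on the distance from the mean T1 ratio to P2 = P1, for instance, yields no usable margin if that mean is at or above 1.
- **Disclosure.** State what 30 per arm can deliver: with a true difference of zero and no covariate adjustment, about 95% power at ±0.94 SD, 84% at ±0.8 SD and 21% at ±0.5 SD. Adjustment for T1 may improve this by an amount that cannot be computed from the article.
- **Fallback.** If no Δ that the trial can support is justifiable, drop the words *equivalence*, *safe* and *no changes*, and report the estimate with its confidence interval as exploratory.

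Cost: new analysis wording and agreement on one margin, with no new procedures. The equivalence claim becomes harder to make, and with a tight margin the trial would probably be inconclusive at its present size. Under the same assumptions, 95% power would need 105 per arm at ±0.5 SD.

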**Methods:**

Sixty patients aged ≥ 18 years, with clinical diagnosis of acute stroke, confirmed by neuroimaging examination, with onset of symptoms within 72 h, under mechanical ventilation through tracheal tube, will participate in this study. Participants will be randomly allocated into 2 groups: experimental group (*n* = 30)—MHM plus tracheal aspiration—and control group (*n* = 30)—tracheal aspiration only. Intracranial compliance will be measured by a non-invasive technique using Brain4care BcMM-R-2000 sensor. This will be the primary outcome. Results will be recorded at 5 times: T0 (start of monitoring), T1 (moment before MHM), T2 (moment after the MHM and before tracheal aspiration), T3 (moment after tracheal aspiration), T4, and T5 (monitoring 10 and 20 min after T3). Secondary outcomes are respiratory mechanics and hemodynamic parameters.

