**Fig. 2 Fig2:**
[figure not shown]
Schematic drawing of experimental design. T0 to T5 represents the assessment stages. DD, dorsal decubitus; EG, experimental group; MHM, mechanical hyperinflation maneuver; CG, control group

Assessments will range five stages: T0 (monitoring start), T1 (before ventilation maneuver for the intervention or control groups), T2 (end of ventilation maneuver our control), T3 (after tracheal aspiration), and T4/T5 (monitoring after 10 and 20 min of procedure). The five initial minutes are required for the initial collection of hemodynamic, ventilation, and neurological data. After the start of this period is T1 with a 10-min duration, followed by T2 and T3, with a 5-min duration each. The individuals in T1 who constituted the MHM group will have their ventilation parameters altered for 10 min according to the lung hyperinflation maneuver adopted, subsequently returning to the baseline values. During this period, the individuals in the control group will be only monitored. In T2, both groups will be subjected to tracheal aspiration; subsequently, data will be monitored for 5 min. Finally, the individuals of both groups were monitored at T4 and T5, 10 and 20 min after the procedure, respectively, to verify vital data stabilization (Fig. 2).

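### The ANOVA admission rule checks normality and equal variances but not sphericity, so the group-by-time test and Tukey comparisons can be miscalibrated if no correction is applied

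*Protocol article*

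**What the plan says.** The Statistical methods section of the protocol article plans, for both outcome sets, "analysis of variance (ANOVA) two-way for repeated measures with the Tukey post-test for results that present normal distribution and homogeneity of variances", with the two conditions "verified by the test of Shapiro–Wilk and Average in Levene, respectively". It names no sphericity check, no epsilon correction and no covariance structure. On the error rate it says "The level of significance established was" p ≤ 0.05. The following paragraph says that the research hypotheses will be tested by non-parametric methods.

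The Primary outcome section fixes the occasions: "In this study, the evaluations will be carried out in five (T1–T5) moments". It ranks them: "The moment of evaluation T2 is the most relevant for the primary outcome", and "as for the secondary outcomes, evaluations from T2 to T5 are the most relevant". The text under Figure 2 gives the early timing as "T1 with a 10-min duration, followed by T2 and T3, with a 5-min duration each", and the abstract gives the later timing as "T4, and T5 (monitoring 10 and 20 min after T3" (minutes counted from T3).

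**The concern.** A within-patient F test with unadjusted degrees of freedom needs the differences between any two times to have the same variance. Shapiro–Wilk looks at distribution shape. Levene, as ordinarily used, compares spread between groups. Data can pass both and still violate sphericity, so the rule as written admits data for which the named test does not hold its level.

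There are two reasons to expect a violation. Readings a few minutes apart usually correlate more strongly than readings half an hour apart. Also, between T1 and T2 only one arm has its ventilator settings changed, so patients may respond differently and spread may rise at T2.

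Two things are at stake. The overall group-by-time test may reject too often. Tukey comparisons that share one pooled error may be too strict for some pairs of times and too lenient for others. With only two arms, a Tukey procedure has nothing to add between arms, so it must concern times or arm-by-time cells, where the pooled error matters. Repairing only the T2 analysis of the primary outcome would leave the secondary outcomes exposed, since they draw on T2 to T5.

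**Working it through.** **Inputs from the article.** Two arms of 30; five times; significance level 0.05; gaps of about 10, 5, 10 and 10 minutes, read as 0, 10, 15, 25 and 35 minutes for T1 to T5. That timetable is a reading of the text: the text under Figure 2 places aspiration in T2, while the Control group section places it in T3.

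**Assumption.** No within-patient correlation is reported. Equal variances and a correlation of ρ^(gap/10) are assumed, with ρ = 0.5 to 0.9 per 10 minutes. Compound symmetry (correlation 0.6) is the reference, and a case with the SD doubled at T2 is added.

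**Step 1: reference.** Uncorrected degrees of freedom are 5 − 1 = 4 and 4 × (60 − 2) = 232. Under compound symmetry the simulated type I error is about 5.1%, so the nominal 5% is reproduced. Unequal spacing alone therefore does no harm.

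**Step 2: how unequal the difference variances are.** With unit variance, Var(Yi − Yj) = 2(1 − ρij). The pooled error reflects the average over all ten pairs.
- ρ = 0.9: T1–T2 gives 2(1 − 0.9) = 0.20. T1–T5 gives 2(1 − 0.9^3.5) = 0.617. The average is 0.321. Ratios to the average: 0.62 and 1.92.
- ρ = 0.5: T1–T2 gives 2(1 − 0.5) = 1.00. T1–T5 gives 2(1 − 0.5^3.5) = 1.823. The average is 1.279. Ratios: 0.78 and 1.43.

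**Step 3: group-by-time test under no effect** (40,000 simulated trials per setting). Greenhouse–Geisser multiplies both degrees of freedom by an estimate of epsilon; at ε = 0.58 they become about 2.3 and 135.

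| ρ per 10 min | ε | Uncorrected | Greenhouse–Geisser |
|---|---|---|---|
| 0.5 | 0.78 | 6.3% | 4.7% |
| 0.7 | 0.68 | 7.1% | 4.7% |
| 0.9 | 0.58 | 8.1% | 4.9% |

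Repeat simulations gave 6.3% to 6.6% at the low end and 8.0% to 8.2% at the high end.

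**Step 4: pooled-error Tukey comparisons of the five time means.** Under sphericity each pair rejects falsely about 0.6% of the time.
- ρ = 0.9: T1–T2 0.06%, T1–T5 4.8%.
- 0.7 per 5 minutes (0.7² = 0.49 per 10 minutes): T1–T2 0.2%, T1–T5 2.2%; family-wise error 5.9%.
- 0.95 per 5 minutes (0.95² ≈ 0.90 per 10 minutes): family-wise error 7.6%.

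**Step 5: spread rising at T2.** With correlation 0.6 and the SD doubled at T2 only, Var(T1 − T2) = 1 + 4 − 2 × 0.6 × 1 × 2 = 2.6. Pairs without T2 have 2(1 − 0.6) = 0.8. The average is (4 × 2.6 + 6 × 0.8)/10 = 1.52, so the T1–T2 ratio is 2.6/1.52 = 1.71. T1–T2 now rejects falsely 3.6% of the time, the uncorrected F 7.3%, and the Tukey family-wise error is 8.1%. The direction of the T1–T2 error has reversed.

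**The case against.** The strongest reply is that the article never says the F test will be uncorrected or that Tukey will use a pooled error. The named software offers the correction, and a condensed article may leave it to a document that is not shown. This limits the point but does not remove it. The article did not stay silent on assumptions: it states the conditions for using the ANOVA, and that list omits the one condition particular to repeated measures.

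Four further objections stand in part.
- The size depends on assumed correlations and an inferred timetable; under compound symmetry there is no inflation.
- The excess is modest, about 1 to 3 percentage points over the assumed range, in a trial that also calls itself exploratory.
- The Tukey figures describe changes over time, whereas the main question is arm against arm at T2. No error rate was computed for that contrast.
- The same section says hypotheses are tested non-parametrically, so it is unclear whether the ANOVA decides anything. It nevertheless remains the stated method for both outcome sets.

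A reader might infer that the trial's error rate will be inflated, or that the method leans towards the hoped-for finding of no change at T2. The documents support neither. The first needs an uncorrected test and a correlation pattern the article does not report. The second holds for T1–T2 under decaying correlation but reverses if spread rises at T2, so no direction is established.

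**Conclusion.** The point holds in conditional form. The stated admission rule cannot detect a failure of sphericity, which is likely in these data. If no correction is applied and correlation decays by a factor of 0.5 to 0.9 per 10 minutes at about 0/10/15/25/35 minutes, the group-by-time test runs at about 6.3% to 8.1% instead of 5%. Pooled-error Tukey comparisons are then miscalibrated pair by pair: T1–T2 is too conservative and T1–T5 too liberal, with T1–T2 too liberal instead if variability rises at T2. Greenhouse–Geisser brings the overall test back to about 5%. Severity is minor to moderate: the inflation is small and assumption-dependent, but it touches both outcome sets and is cheap to prevent.

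**What to change.** In Statistical methods, wherever the ANOVA is to be used:
- Replace it with a mixed model for repeated measures with unstructured covariance, treating T1 as baseline. At minimum, commit to Greenhouse–Geisser-corrected F tests.
- Replace pooled-error Tukey with between-arm contrasts, each with its own standard error: at T2 for the primary outcome, and at T2 to T5 with a multiplicity adjustment for the secondary outcomes. T1 precedes the intervention and should not be among the tested times.
- State how this analysis relates to the sentence on non-parametric testing, so that one method is named for each hypothesis.
- Note that tests of difference, corrected or not, do not by themselves show equivalence, which is the design the article declares.

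The cost is analysis wording and a few degrees of freedom for the covariance. SPSS 22, the named software, offers both the correction and the mixed model. No change to data collection or sample size is needed.
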